## Abstract

Background: in this protocol we outline a method of working alongside Aboriginal communities to learn about and facilitate improvement in the oral health habits in Aboriginal adolescents. By facilitating positive oral health in Aboriginal adolescents, we hope to achieve lifelong improvement in oral health and general wellbeing. Methods: this paper outlines a co-design methodology through which researchers and Aboriginal communities will work together to create a custom oral healthcare program aimed at Aboriginal adolescents. Researchers, a youth advisory group, Aboriginal community-controlled health services and three regional NSW communities will together devise an oral health strategy focused on five components: application of topical fluoride, increasing water consumption, improving nutrition, daily toothbrushing, and enhancing social and emotional wellbeing. Capacity building is a key outcome of this program. Discussion: as the gap in health status between Aboriginal and non-Aboriginal people remains wide, it is clear that new approaches and attitudes are needed in Aboriginal public health research. This protocol is representative of this shifting approach; giving power to Aboriginal communities who seek to have sovereignty and self-determination over their healthcare. Trial registration: TRN: ISRCTN15496753 Date of registration: 20 October 2021.

## 1. Introduction

In Australia, a gap exists in health outcomes between Aboriginal and Torres Strait Islander people (hereafter referred to as Aboriginal people) and other Australians. Many studies examine and quantify the facets of ill-health in Aboriginal people [1]. This deficit discourse in the literature, without offering culturally safe solutions, contributes to feelings of shame and stigma among Aboriginal communities [1]. New approaches are needed which use the strengths of Aboriginal communities to collaboratively produce health promotion programs to positively impact the determinants of health for Aboriginal people.

Health-related behaviours can be major causes or preventers of serious morbidity. Health-related behaviours that begin in adolescence affect a person’s health both in the current stage of life and throughout adulthood [2]. This protocol defines adolescence as ages 10–19 in line with the World Health Organisation definition [3]. Oral health and oral hygiene behaviours also contribute to overall wellbeing and have a substantial influence on overall health [4]. Periodontal (gum) disease is associated with many systemic conditions including cardiovascular disease [5], pneumonia and kidney disease [6]. A strong bidirectional relationship also exists between periodontal disease and diabetes [7].

In terms of oral health, Aboriginal adolescents have a greater average number of dental caries and receive more frequent tooth extractions compared to their non-Aboriginal peers [8,9]. Aboriginal people are less likely to receive timely preventative dental treatment [10] and are more likely to be hospitalised due to oral health infections and disease [8]. This can be attributed to many of the social and cultural determinants of health [10]. Few studies have effectively examined or sought to change oral health outcomes for Aboriginal adolescents during these formative years [11].

A recent systematic review found that successful oral health interventions for Indigenous people globally adopted culturally safe, participatory and collaborative approaches [12]. It concluded that an effective program should employ local workers, utilise multiple settings and strategies and address the social, economic and cultural determinants of health [12]. Despite this, few oral health research papers have explored social determinants of health in this context or established career development pathways for local workers despite many claiming to adopt a ‘capacity building’ approach [12].

High strength fluoride varnishes given to children two to four times per year are associated with a significant reduction in the development of future dental caries by up to 43% [13]. In New South Wales (NSW), high strength fluoride varnish may be applied by dentists, dental therapists, oral health therapists and dental hygienists [14]. Non-registered oral health workers such as dental assistants may apply fluoride varnish following specific training and approval from relevant regulatory authorities [15]. A previous study demonstrated the feasibility of utilising oral health therapists to apply fluoride regularly to Aboriginal children in rural schools in NSW [16]. This study also noted the employment of dental assistants to apply fluoride varnish. This would improve sustainability, build community capacity, and increase potential reach of such a program which provides an important link to this study [16]. The application of fluoride varnish together with locally designed strategies to encourage tooth brushing will be critical when designing preventative health promotion initiatives.

Tooth brushing is a central component of achieving and maintaining good oral health. Despite this, only 54.5% of adolescents in NSW report that they brush their teeth twice or more per day [17]. Furthermore, adolescents in NSW who brush their teeth twice a day have fewer decayed, missing or filled teeth compared to those who do not (0.91 vs. 1.46 teeth) [17]. A survey in Central Northern NSW found that only 12.8% of Aboriginal children aged 5–12 years reported brushing their teeth the morning before the survey and 64.1% reported owning a toothbrush at home [18]. A co-designed, school-based program was effective at increasing rates of tooth brushing among children in the region [19]. The authors noted that community ownership was important in ensuring the success and sustainability of the program [19]. Despite this success, no subsequent studies have sought to adapt a tooth brushing initiative aimed towards Aboriginal adolescents in Australia. Continuity of tooth brushing, and dental health education is needed to ensure Aboriginal adolescents maintain good oral health habits into adulthood.

The consumption of sugar-sweetened beverages is associated with an increased risk of dental caries in children and poorer metabolic health, and high among Aboriginal adolescents [20]. Adolescents in NSW who regularly consumed one or more sugary drinks per day had a greater number of decayed missing or filled teeth compared to those who did not (1.21 vs. 0.8 teeth) [17]. The Australian dietary guidelines recommend the consumption of fluoridated tap water and the limiting of sugar-sweetened beverages such as soft drinks, cordials, fruit juices and sports drinks [21]. Australian rural communities experience high temperatures in summer months. Taste aversion, poor water quality and inaccessibility to free refrigerated and filtered water can leads adolescents to opt for store-bought sugar sweetened beverages over tap water [19]. A study in Central Northern NSW installed refrigerated and filtered water fountains in key community locations as part of a suite of preventive strategies to improve oral health [19]. As a result, children reported consuming fewer sugar-sweetened beverages [19]. Novel approaches such as this are needed to increase the consumption of fluoridated tap water and decrease the consumption of sugar-sweetened beverages.

Dietary risk factors are estimated to contribute to 9.7% of the burden of disease in Australia’s Aboriginal population [22]. Among Aboriginal Australians, high school-aged adolescents were the least likely to meet the National Health and Medical Research Council (NHMRC) guidelines for consumption of fruit and vegetables [23]. In 2012–2013 only 21% of Aboriginal adolescents aged 15–17 years met the dietary guidelines for adequate fruit intake while 2.8% met the recommended intake of vegetables [23]. This indicates that Aboriginal adolescents may require additional support to meet dietary guidelines. Diet and eating patterns play a significant role in the development of oral disease thus dietary education should be included in a successful oral health program [24]. A 2013 Japanese study found participation in a dietary education program in high school correlated with a reduction in dental caries in early adulthood [25].

The current standard of health service delivery has been ineffective in closing the gap between the health outcomes of Aboriginal and non-Aboriginal people [26]. Health programs designed for the general population often fail to meet the needs of Aboriginal communities, especially adolescents. Effective healthcare for Aboriginal people must have a consistent focus on cultural competence and strong organizational, community and clinical governance [26]. The National Aboriginal and Torres Strait Islander Health Implementation plan also outlines the strategic need to involve adolescents in the planning and implementation of strategies addressing their health needs [27]. Co-design is a process which requires active involvement of all stakeholders. Co-design is not merely consultation or participant approval; but a methodology where the beneficiaries of the project or research participate in every step of the process from conception to design, implementation and evaluation [28]. In the context of Aboriginal health, co-design seeks to ensure a health program is created which is responsive to the unique needs of local Aboriginal people [28]. Co-design also helps gain necessary collective buy-in of the community and leads to higher rates of uptake and involvement and thus contributes to improved health outcomes [28]. This paper describes the protocol for a co-designed, culturally safe, evidence-informed approach to improving the oral health of Aboriginal adolescents within a wider social determinants approach.

## 2. Materials and Methods

The Indigenous Adolescent Oral Health Partnership Study is an implementation science project using a co-designed, multidisciplinary, mixed methods approach in collaboration with Aboriginal communities in NSW, Queensland and Victoria, Australia. It involves a partnership between tertiary education institutions, Aboriginal Community Controlled Health Services (ACCHS), professional organisations, industry and health care providers. Partners will provide expertise, in-kind support or guidance throughout the study. The study will comprise three broad phases including: planning, implementation, and analysis. Co-design methodology will be embedded throughout each phase.

In 2019, a video was produced by the Poche Centre for Indigenous Health at the University of Sydney with Aboriginal people from NSW who were undertaking vocational training in Dental Assisting. The purpose of this video was to promote participation in a questionnaire to identify possible oral health promotion strategies for Aboriginal adolescents. Prior to participating in the questionnaire, participants were issued a study information statement and signed a consent form. The results of this pre-pilot questionnaire, as well as recommendations of a literature review examining successful components of oral health interventions for Indigenous adolescents globally, have led to the development of five core oral health aims for this study. These include: (1) increasing topical fluoride application; (2) increasing tooth brushing (3) increasing the consumption of water; (4) improving nutrition behaviours; and (5) enhancing social and emotional well-being among Aboriginal adolescents in communities in NSW, Queensland and Victoria. This study will take place over five years (2022–2027) and across three phases. These phases include (1) Planning (2022–2023); (2) Implementation (2023–2025); and (3) (2025–2027). Figure 1 demonstrates the three phases of this study.

We hypothesise that involving Aboriginal and Torres Strait Islander adolescents in the design and delivery of evidence-based oral health promotion strategies will improve the oral health and social and emotional wellbeing of Aboriginal and Torres Strait Islander adolescents.

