### 2.6. Data Collection

Baseline oral health status of participants will be recorded by the co-researcher from the local ACCHS. A co-researcher who is a registered dental practitioner will record the number of teeth and the presence of dental caries into the participant’s electronic medical record using Titanium dental software (Titanium Solutions, Auckland, New Zealand). Participating adolescents will also be asked to complete a questionnaire to determine their baseline oral health habits. This questionnaire will be administered by the Aboriginal co-researchers and collect information on the participant’s demographics, perceived overall oral health, oral hygiene routine, brushing frequency, consumption of sugar-sweetened beverages and past dental treatments. In order to minimise recall bias an existing validated oral health questionnaire will be used as a guide, We will work with the YAG to ensure the questionnaire is culturally safe. The dental screening and questionnaire will also be completed at the conclusion of the oral health program for comparison. Data collected will also be compared to any locally available individual clinical data with participant or guardian consent. Comparison of summary data will also be made with existing state and national data sets on oral health and hygiene behaviours of adolescents.

Co-researchers will also collect data on the uptake and efficacy of each strategy. This will include the number of fluoride varnish applications for each participant, utilisation of the toothbrush tracking program and water fountain usage meter readings. The co-design methodology will allow co-researchers, participating dental assisting students and participating adolescents to provide input on strengths and weaknesses of the oral health program continuously and make changes to the protocol as required to ensure the implementation of strategies remains relevant and meets the needs of the local community.

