### 2.8. Analysis Phase

Quantitative data on oral health status and oral health habits of participating adolescents will be analysed using statistical analysis software (IBM SPSS Statistics Version 26) to examine and quantify changes in oral health status at the completion of the oral health program. These results will also be compared with NSW and National figures from the NSW Teen Dental Survey and the National Child Oral Health Survey. Qualitative data regarding utilisation and engagement will be analysed thematically to determine the overall utility and acceptance of each section of the oral health program. This analysis will inform the future expansion, development or removal of components of the oral health program and recommendations for future oral health promotion strategies targeting Aboriginal adolescents.

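### The hypothesis claims improved social and emotional wellbeing, but no listed measure or analysis captures change in wellbeing

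*Protocol article*

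**What the plan says.** Section 2 (Materials and Methods) states a hypothesis with two outcomes: the approach "will improve the oral health and social and emotional wellbeing of Aboriginal and Torres Strait Islander adolescents". Of the five core aims in the same section, the last three read "3) increasing the consumption of water; (4) improving nutrition behaviours; and (5) enhancing social and emotional well-being among Aboriginal adolescents". The Discussion again presents wellbeing as a central focus, and the Abstract adds: "Capacity building is a key outcome of this program".

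Section 2.6 sets out the measures. A registered dental practitioner "will record the number of teeth and the presence of dental caries into the participant’s electronic medical record". A questionnaire covers demographics plus "perceived overall oral health, oral hygiene routine, brushing frequency, consumption of sugar-sweetened beverages and past dental treatments". Both are repeated: "The dental screening and questionnaire will also be completed at the conclusion of the oral health program for comparison". The section goes on: "Co-researchers will also collect data on the uptake and efficacy of each strategy". The items it then names are varnish applications per participant, use of the toothbrush tracking program, and fountain meter readings.

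On analysis, section 2.8 begins: "Quantitative data on oral health status and oral health habits of participating adolescents will be analysed". The stated purpose is to quantify change in oral health status. A thematic qualitative analysis of use and engagement follows, to judge how useful and acceptable each component was.

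**The concern.** A hypothesis that names two outcomes needs a measure of each, taken at baseline and again at the end. Here the article is specific about what is measured, and that list leaves out the second outcome.

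If the list is followed, the peer-led buddy program will be delivered without before-and-after data on the thing it is meant to change. Section 2.8 says the results will guide whether components are expanded, developed or removed. For the wellbeing component, that decision would rest on use and acceptance alone. A baseline that is not taken cannot be reconstructed afterwards.

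**Working it through.** No arithmetic applies. The target of 60 participants is justified by diversity and carries no power calculation to reproduce. The check sets each stated claim against the measures named in section 2.6 and the analyses named in section 2.8.

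| Claim | Named measure (2.6) | Named analysis (2.8) | Result |
|---|---|---|---|
| Hypothesis, limb 1: oral health | Dental screening and questionnaire, start and end | Quantitative change | Testable as before-and-after change |
| Hypothesis, limb 2, and aim 5: wellbeing | None | Acceptance of the component only | Not testable as described |
| Aim 1: topical fluoride | Applications per participant | Not itemised; measure exists | Measured |
| Aim 2: toothbrushing | Questionnaire at both times; tracking program | Habits | Measured |
| Aim 3: water | Fountain meters; sugary-drink item as proxy | Habits, through the proxy | Partly measured |
| Aim 4: nutrition | Sugary-drink item only | Habits, through the proxy | Thinly measured |
| Capacity building (Abstract) | None | None | No named indicator |

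1. **Wellbeing.** No questionnaire topic in section 2.6 is a wellbeing topic. The instrument used as a guide is an oral health questionnaire, so nothing stated implies that a wellbeing scale comes with it. The qualitative arm can show whether adolescents liked and used the buddy program. It does not measure whether their wellbeing changed.

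2. **The general promise.** The sentence quoted last from section 2.6 covers all five strategies. The three items that follow it are measures of use, and they belong to strategies 1 to 3. Nothing is named for strategy 4 (nutrition education) or strategy 5 (wellbeing).

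3. **Water.** A fountain meter records use of the fountain by anyone, so a reading cannot be attributed to participants. A newly installed fountain has no earlier reading. Section 2.2 leaves installation to be discussed in the workshops.

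4. **Nutrition.** The Introduction argues for dietary support from fruit and vegetable intake: 21% and 2.8% of Aboriginal adolescents aged 15–17 met the respective guidelines. Neither food group is among the listed items.

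**The case against.** There is a fair case on the other side, and parts of it stand.

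- **The list is open.** Section 2.6 promises data on every strategy, and the items that follow are introduced as inclusions, not as a complete list. This stands: the right wording is that no wellbeing measure is named, not that none will exist. It does not close the gap, because neither a measure nor a wellbeing baseline is described.
- **This is a journal article, and co-design defers detail.** The full protocol is not shown, the questionnaire is to be worked through with the YAG, and the Limitations say some elements stay open until the YAG and workshops meet. Planning (2022–2023) comes before implementation (2023–2025), so nothing shows that a baseline has been lost. This stands as a caution. But the article is not silent on measurement: it itemises topics and analysis targets, and those do not match its own hypothesis. The role it gives the YAG on the questionnaire is to ensure cultural safety, which is compatible with committing now to measure wellbeing.
- **Water and nutrition are not unmeasured.** The Introduction reports lower sugary-drink consumption after fountains were installed in an earlier study, so the sugary-drink item is a reasonable indicator for strategy 3 and is also a dietary behaviour. This stands, and it makes these items secondary.
- **Capacity building is in neither the hypothesis nor the five aims.** This also stands. Elsewhere the article treats it as a benefit that the program delivers. The lack of an indicator is a reporting gap against the Abstract and does not make a hypothesis untestable.

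A reader might go further and infer that the study cannot answer its own question at all. The documents do not support that. The oral health limb has clinical and questionnaire data at both time points and a stated analysis.

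**Conclusion.** The concern holds for wellbeing. One of the two outcomes in the hypothesis, which is also one of the five aims, has no named measure and no named analysis of change. As described, that limb cannot be tested, and neither can the hypothesis taken as a whole. The oral health limb is unaffected by this point.

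The gaps for water, nutrition and capacity building are real but smaller. The first two have proxy or partial measures, and the third lies outside the hypothesis.

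The conclusion assumes that the topics listed in section 2.6 and the targets listed in section 2.8 reflect what is planned. If the full protocol or the YAG-reviewed questionnaire already contains a wellbeing scale at both time points with a matching analysis, the point reduces to correcting the article.

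**What to change.** **Main change, one of two:**

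- Before the first baseline, add a short wellbeing scale endorsed by the YAG to the questionnaire at both time points. Name it in section 2.6, and list change in wellbeing as an analysed outcome in section 2.8.
- If wellbeing will not be measured, remove it from the hypothesis. The buddy program can then be described as a component assessed for use and acceptance.

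**Secondary and optional:**

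- Add one participant-level item on water intake and brief fruit and vegetable items, agreed with the YAG. Any comparison with the 21% and 2.8% figures would apply only to participants aged 15–17, since the study enrols ages 10–19.
- Report capacity building from training and employment records, for example the numbers starting and completing the dental assisting certificate, the varnish unit and the community research skill set, and the numbers employed as co-researchers.

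**Cost:** a somewhat longer questionnaire at two administrations that are already planned, so a small added respondent burden, plus a count from existing records. The documents give no figure for the time involved. Narrowing the hypothesis costs only an edit, but it gives up the claim about wellbeing.

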### 2.1. Planning Phase

The planning phase will involve the establishment of a youth advisory group (YAG) to guide the study at each stage, meeting quarterly over the two-year study period. The YAG will be established by the Poche Centre for Indigenous Health in conjunction with representatives from The Matilda Centre for Research in Mental Health and Substance Use, the NSW Aboriginal Health and Medical Research Council (AH&MRC) and the Black Dog Institute; as well as eight Aboriginal people aged 10–19 years from Aboriginal communities across Australia.

During this phase, Aboriginal people undertaking vocational training in Dental Assisting (Qualification: Certificate IV in Dental Assisting [oral health promotion]) will be invited to be co-researchers in this study. As co-researchers they will be offered to complete a separate vocational qualification on research in communities (Qualification: Skill Set in Community Research). This qualification will cover basic research methodologies and data collection to enable co-researchers to collect data systematically.They will also be trained in the application of fluoride varnish and assist in the development of oral health promotion strategies such as tooth brushing and toothpaste distribution that will be included in the implementation phase of the study, under the supervision and guidance of oral health practitioners from the local ACCHS who have partnered with this study.

Co-researchers will conduct co-design workshops as part of the planning phase within the three participating communities in NSW, Queensland and Victoria to enable Aboriginal adolescents, families, community members and Elders to work with researchers to develop and refine an oral health program that is specific to the needs and customs of their particular community. The co-design process will likely include yarning and other Indigenous research methodologies. The oral health program will include key strategies that are based on the five core oral health aims of this study.

